**Methods/design:**

Forty participants will be randomly assigned to the acupuncture plus usual care group or the usual care control group. The acupuncture plus usual care group will undergo treatments on seventeen acupuncture points, three times per week for four weeks. The control group will receive only usual care during the same period. The primary outcomes will be scores on the Ocular Surface Disease Index (OSDI) and the results of examinations at 1, 3, 5, and 13 weeks. The secondary outcomes will be Tear Film Break-up Time (TBUT), as well as scores on the Schirmer-I test, visual analog scale (VAS), and quality of life (QOL) questionnaire for the self-assessment of ocular discomfort. Digital photographs will be taken to document the pattern of fluorescein staining observed on the corneal surface. The results of the Schirmer-I test, TBUT, and fluorescein-stained corneal surface digital photographs will be assessed at the screening and at week 13. VAS scores will be assessed at the screening, as well as at 1, 3, 5, and 13 weeks. QOL will be evaluated at 1, 3, 5, and 13 weeks.

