### Randomization and allocation concealment

For randomization and allocation concealment, a set of random numbers will be generated using computerized SAS block-randomization software (SAS® version 9.3, SAS Institute, Inc., Cary, NC, USA). Sealed, opaque assignment envelopes will be used for allocation concealment [16].

The primary data collected will be used to investigate the impact of expectations on the success of acupuncture treatment. Because participant expectations could affect treatment outcomes, each patient will be queried regarding their perception of acupuncture therapy prior to group allocation [17]: 'How much do you expect that the acupuncture treatment will relieve your dry eye symptoms?’ Participants will be asked to select one point on a 10-point Likert scale (0 not useful to 9 very useful).

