### Statistical analysis

Because this is an exploratory pilot study designed to evaluate the feasibility of acupuncture for the treatment of dry eye syndrome after refractive surgery, sample size was not calculated according to the conventional power analysis method. Twenty subjects will be recruited for each group.

The statistical analysis will be conducted using SAS software (version 9.3, SAS Institute Inc., Cary, NC, USA) with the significance level set at 0.05. Efficacy measurements were adjusted by intention to treat analysis (ITT). Missing values will be imputed by the last observation carried forward (LOCF) method. Analysis of covariance (ANCOVA) will be used to test measured outcomes (OSDI, TBUT, Schirmer-I test, QOL and VAS for the self-assessment of ocular discomfort). ANCOVA will be used to determine whether dependent variable values are equivalent across levels of a categorical independent variable by statistically controlling for the effects of other variables known as covariates. The change in scores for each group will serve as the dependent variable, the baseline scores will serve as covariates, and the group will serve as the fixed factor. The Chi-square test or Fisher’s exact test will be used to identify any differences among groups in fluorescein staining of the corneal surface.

Using this correlation analysis, we will evaluate the relationship between patients’ expectations of acupuncture treatment and the relief of dry eye symptoms in the acupuncture plus usual care group.

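### The planned expectation analysis, a correlation within the acupuncture arm, can describe an association but cannot answer the stated aim about the success of acupuncture

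*Protocol article*

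**What the plan says.** Three statements in the protocol article matter.

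- **Aim** (Randomization and allocation concealment): "The primary data collected will be used to investigate the impact of expectations on the success of acupuncture treatment". The reason given is "Because participant expectations could affect treatment outcomes".
- **Measurement** (same section): "each patient will be queried regarding their perception of acupuncture therapy prior to group allocation", on a single item scored 0 to 9. Because the question comes before allocation, it is put to patients of both arms.
- **Analysis** (Statistical analysis): a correlation analysis of the relationship between patients' "expectations of acupuncture treatment and the relief of dry eye symptoms in the acupuncture plus usual care group".

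The same section describes the efficacy model: an ANCOVA of change, with baseline score as covariate and group as fixed factor. Expectation is not in it. No analysis described in the article uses the control arm's expectation scores.

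**The concern.** The success of acupuncture in this trial means its benefit over usual care, since that is the contrast the randomisation sets up. Two different mechanisms would both produce a positive correlation among acupuncture patients:

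1. Expectation changes how much acupuncture adds to usual care.
2. Patients with high expectations improve, or report improvement, whatever care they receive.

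Only the first bears on the aim as worded. The second is ordinary prognosis or reporting style. A correlation computed in one arm contains no information that separates them. The control arm does carry some, because its patients answered the same question before knowing their allocation, yet the plan leaves those scores unused.

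What is at stake is the interpretation of a secondary result. A significant correlation could be reported as evidence that expectation drives response to acupuncture when the data would look the same if it did not. The question is a real one here: there is no sham procedure, so participants know their arm, and the primary outcome (OSDI) is patient-reported.

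**Working it through.** **Inputs from the protocol article**

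- "Forty participants will be randomly assigned to the acupuncture plus usual care group or the usual care control group"; "Twenty subjects will be recruited for each group". Check: 20 + 20 = 40.
- Significance level 0.05 (Statistical analysis); the sidedness is not stated, and two-sided is assumed.
- The article gives no expected correlation, SD or power, so there is no figure of its own to reproduce.

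**Assumptions.** Normal data; correlations between expectation and improvement from 0.2 to 0.6. These are illustrative values, shown as a range.

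**Step 1. Precision of the planned correlation, n = 20**

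- Smallest significant |r|: t / √(18 + t²) with t = 2.101 on 18 degrees of freedom, which is 2.101 / √(18 + 4.414) = 0.44.
- 95% CI by Fisher's z: tanh(atanh(r) ± 1.96/√17), where 1.96/√17 = 0.475. Around r = 0 this is −0.44 to 0.44. Around r = 0.3 it is tanh(0.310 ± 0.475), or −0.16 to 0.66.

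**Step 2. Can the planned test tell the two mechanisms apart?**

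Trials with 20 patients per arm were simulated (20,000 to 100,000 per scenario). The planned test is the correlation in the acupuncture arm. The comparison is a test of the difference between the two arms' expectation slopes in all 40 patients (36 residual degrees of freedom, without a baseline covariate).

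Expectation predicts improvement equally in both arms, so it does not modify the treatment effect:

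| Correlation in both arms | Planned test significant | Slope difference significant |
|---|---|---|
| 0.2 | 13–14% | 5% |
| 0.3 | 25% | 5% |
| 0.5 | 64% | 5% |
| 0.6 | 83–84% | 5% |

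Expectation matters only under acupuncture (correlation 0 in controls):

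| Correlation in acupuncture arm | Planned test significant | Slope difference significant |
|---|---|---|
| 0.3 | 25–26% | 15% |
| 0.5 | 64% | 34–39% |
| 0.6 | 83–84% | 48–58% |

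The planned test's column is the same in both tables. This follows from the design of the test, since it never looks at the control arm. The ranges for the slope difference reflect the variance assumption: the lower figure takes equal total variance in the two arms, the higher takes equal residual variance.

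**Step 3. Is the slope difference itself a clean answer?**

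Suppose expectation is unrelated to improvement under acupuncture, but controls with high expectations are disappointed and report worse results. With a correlation of 0 against −0.3 / −0.5, the slope difference is significant in about 15% / 34% of trials (15% / 39% with equal residual variance), while the planned acupuncture-arm test stays at 5%. The slope difference is therefore informative but not specific to a change in the benefit of acupuncture.

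**The case against.** The Statistical analysis section, read alone, promises only to evaluate a relationship, and names its population. A within-arm correlation does that. If expectation truly correlates 0.5 with relief in that arm, a significant result is a correct detection, and 64% is power. This stands: the percentages in the first table are not false-positive rates of the test as specified. They mislead only if the result is read as answering the aim in the randomisation section.

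It can also be said that the control arm is not a clean reference. The item asks about acupuncture, which controls do not receive, and Step 3 shows that disappointment alone can produce a difference in slopes. This stands too. A reader might infer that the interaction test would settle the question and that the planned analysis is wrong by comparison. The documents do not support that: expectation is not randomised, participants know their arm, and 20 per arm gives low power. An interaction would indicate effect modification at most, not causation.

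A reader might further object that the correlation is not adjusted for baseline, or that the reference to *this* correlation analysis points to nothing earlier in the text. The first is a detail that a condensed article may leave to the full protocol or analysis plan. The second is an editorial slip. Neither is part of this point.

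What the objections leave intact is the mismatch between the aim and the one analysis stated, and the fact that data bearing on the aim are collected in both arms and used in one.

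**Conclusion.** The point holds as a minor one. The aim speaks of the impact of expectation on the success of acupuncture. The stated analysis can show only whether expectation and relief go together among acupuncture patients. It is significant equally often whether expectation merely predicts improvement or matters only under acupuncture: about 25% of trials at an assumed correlation of 0.3, 64% at 0.5 and 83% at 0.6.

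The argument that one arm cannot separate the two mechanisms does not depend on these values; the percentages do. They rest on assumed correlations, normal data and a two-sided 0.05 test.

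This is an ancillary analysis in an exploratory pilot. The primary treatment comparison is not affected.

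**What to change.** Either of two changes resolves the mismatch.

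**Preferred: use both arms.**

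- Report the slope of OSDI change on expectation, with its 95% CI, in each arm.
- Add expectation (centred) and group-by-expectation to the baseline-adjusted ANCOVA of OSDI change in all 40 patients, and report the interaction estimate with its 95% CI as exploratory.
- Name the visit. OSDI is scheduled at visits 2, 8, 14 and 15, and the article designates none of them as primary. Visit 14, four weeks after visit 2, is one candidate.
- State two caveats with the result: the estimate is imprecise (power about 15% to 48% for correlations of 0.3 to 0.6 against 0, taking equal total variance), and in an open trial it may reflect disappointment among controls as well as a change in the benefit of acupuncture.

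**Alternative: narrow the aim.** Reword the sentence in the randomisation section so that it promises only a description of the association between expectation and relief within the acupuncture arm.

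The cost is wording and a small amount of extra analysis. No new data are needed, because the question is already put to every patient. The price of the preferred option is a wide interval that will seldom be conclusive.

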### Adverse events

Adverse events are unexpected signs, symptoms or diseases encountered during the clinical trial, whether or not they are related to acupuncture treatment. Local, general, and psychological adverse events may be observed. Local symptoms may include continual swelling, redness and itching lasting ≥ three days, peripheral neuritis and hemorrhage, and bruises/pain lasting ≥ two weeks. Systemic symptoms include headaches lasting longer than three days and circulatory problems, including dizziness and palpitations. Psychological problems include hypersensitivity for over three days and anxiety or fear for over 60 hours. All unexpected responses related to acupuncture treatment will be recorded. In order to prevent bias, an expert panel of individuals who are not otherwise connected to this study will evaluate any report of an adverse event. Each report will include a description of any associated symptoms, including the date of onset, the duration, and the degree of severity (Spilker’s criteria [22]: 1 = mild, 2 = moderate and 3 = severe, the patient’s perception of a causal relationship with the treatment (1 = definitely related, 2 = probably related, 3 = possibly related, 4 = probably not related, 5 = definitely not related and 6 = unknown), acupuncture-related action (1 = no change, 2 = temporarily suspend, 3 = suspend), treatment of the adverse event and treatment results. If serious adverse events (SAE) occur, these will be related to the IRB; experimental treatments will be stopped immediately and appropriate treatments will be administered.

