## Intervention

### Acupuncture plus usual care group

The acupuncture plus usual care group will be treated three times per week for four weeks. Each session of treatment will include the use of 17 acupuncture points (bilateral BL2, GB14, TE23, Ex1, ST1, GB20, LI4, and LI11, and single GV23). These will be localized according to the 'WHO Standard Acupuncture Point Location in the Western Pacific Region’ protocol [18]. Four experts in the field of alternative medicine who have trained for at least seven years and practiced for at least three years will perform these treatments using 0.20 mm × 30 mm disposable acupuncture needles (Dongbang Acupuncture Inc., Chungnam, Republic of Korea). The '*de-qi*’ sensation will be induced by twisting acupuncture, and the needles will be retained for 20 minutes before removal. The patients will be allowed to use any additional treatment for dry eye symptoms other than punctal plugs or punctal occlusion surgery. Patients will not be permitted to participate in any other regimen of acupuncture therapy. Any changes in medical history or vital signs and reports of adverse events will be recorded at every follow-up visit.

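### Adverse events are defined, and acupuncture responses recorded, only when *unexpected*, so expected needling reactions need not be reported

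*Protocol article*

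**What the plan says.** The Adverse events section of the protocol article sets the scope in one sentence: "Adverse events are unexpected signs, symptoms or diseases encountered during the clinical trial, whether or not they are related to acupuncture treatment". A later sentence deals with needling in particular: "All unexpected responses related to acupuncture treatment will be recorded". Both contain the same adjective.

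Between them come examples. The local ones are "continual swelling, redness and itching lasting ≥ three days, peripheral neuritis and hemorrhage, and bruises/pain lasting ≥ two weeks". The systemic and psychological examples follow the same pattern: headache beyond three days, hypersensitivity beyond three days, and anxiety or fear beyond 60 hours. Dizziness and palpitations have no minimum.

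The section then describes the report: "Each report will include a description of any associated symptoms, including the date of onset, the duration, and the degree of severity". Severity starts at mild, the patient's "perception of a causal relationship with the treatment (1 = definitely related" and so on down a six-point scale, and the recorded action may be no change. A panel with no other link to the study evaluates each report.

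On exposure, the section on the acupuncture plus usual care group says: "The acupuncture plus usual care group will be treated three times per week for four weeks". It also says: "Each session of treatment will include the use of 17 acupuncture points". The same section has changes in medical history and adverse event reports recorded at each follow-up visit, without giving a wider definition of an adverse event.

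**The concern.** Expectedness is a useful way to classify an adverse event, but a poor condition for recording one. For a needling treatment, the reactions staff are most likely to regard as expected are those the treatment itself causes. A rule that starts from *unexpected* therefore permits their omission in the one arm where needle-specific reactions to study treatment can arise.

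The abstract's Discussion paragraph says the trial will supply first data on safety as well as effectiveness. The main Discussion adds that no earlier study has tested acupuncture in this population and that the results will inform a larger trial. Someone planning that trial who saw few reactions reported could not tell whether few occurred or whether the definition kept them out.

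**Working it through.** The plan states no figure to reproduce: no adverse event rate, no safety sample size and no safety comparison. The check is mainly a reading of the text.

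1. **Definition.** It is wide on relatedness, since events count whether or not acupuncture caused them. It is narrow on expectedness. An expected event falls outside it.

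2. **Recording sentence.** It covers responses related to acupuncture and repeats the restriction. The limit therefore does not rest on a single stray adjective.

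3. **Examples.** Most carry a minimum duration, which fits an intention to set aside ordinary, brief reactions. But the local list is introduced as what symptoms *may* include, and peripheral neuritis, hemorrhage, dizziness and palpitations have no minimum. The durations neither exclude shorter events nor widen the definition.

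4. **Report.** It has room for a mild, definitely related event with no change of treatment. It can hold a minor needling reaction, but nothing obliges anyone to enter one.

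5. **Other routes.** Adverse event reports at follow-up visits take their meaning from the same definition. The medical history item may catch some reactions. However, only adverse event reports are stated to carry onset, duration, severity and causality and to go to the panel.

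No sentence in the article requires an expected needling reaction to be recorded.

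Two pieces of arithmetic give context but do not measure missed events.

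- **Exposure.** Eight bilateral points and one single point give 8 × 2 + 1 = 17 points. Three sessions a week for four weeks give 3 × 4 = 12 sessions. With one needle per point and full attendance (both assumed), 17 × 12 = 204 placements per participant and 204 × 20 = 4,080 in the arm. Controls have none from study treatment.
- **Unit of change.** Let k be the number of acupuncture patients whose only reactions are expected ones that go unreported. The arm's proportion with any event is then too low by k/20, or 5 percentage points per patient. The documents give no information on k, which may be zero.

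**The case against.** The strongest reply is that *unexpected* is loose wording for *untoward* or *unintended*. The article never says which reactions are expected. It goes on to name swelling, redness, hemorrhage, bruises, pain and dizziness as adverse events, and a list of foreseeable events could hardly illustrate a definition confined to unforeseen ones. The report form, with its mild and definitely related categories, points the same way. This reading is plausible, and it stands as a reason for caution about intent. It does not settle the matter: the word appears twice, is undefined, and leaves each assessor to decide.

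A second reply is that a journal article condenses a full protocol, whose recording instructions may be broader. That limits what can be inferred about practice on site. The point, however, concerns a rule the article does state, not a detail it leaves out.

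A third is that this is an exploratory pilot with 20 patients per arm, that safety is not among the listed primary or secondary outcomes, and that serious events have their own route to the ethics board. All of that is true and limits the consequence. It does not help the promised safety data.

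A reader might also infer that the listed durations are cut-offs, so that a bruise clearing in ten days is excluded. The documents do not support that. Bruises are named as adverse events, nothing calls them expected, and the two-week figure belongs to an illustrative list.

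**Conclusion.** The point holds as a matter of wording. Both the definition and the recording sentence are confined to the unexpected, and nothing else in the article requires expected needling reactions to be captured. If staff apply the word literally, the acupuncture arm's safety burden could be understated. If they read it as *untoward*, there is no loss. The text does not say which reading applies.

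The size cannot be computed. It would be tempting to choose a number of affected patients and quote a percentage-point shortfall, or to treat the 4,080 placements as a gauge of missed events. Neither is supported: the first depends wholly on the number chosen, and the second counts needles.

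Nor do the documents show that the comparison between arms as a whole favours acupuncture. The direction is clear only for needle-specific reactions. Redness, itching and pain are also dry eye symptoms in the inclusion criteria and can occur in both arms. The acupuncture arm is also seen more often: three times a week during treatment, against every two weeks for controls. That gives more opportunity to report events and works in the opposite direction.

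The efficacy analysis is not affected. The correction is worth making because it is cheap and bears on an aim the article states.

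**What to change.** Define an adverse event as any untoward sign, symptom or disease during the trial, whether or not it was expected, whether or not it is related to treatment, and regardless of duration. In the recording sentence, replace *unexpected* with *untoward* rather than simply deleting it. The protocol intends a de-qi effect ("sensation will be induced by twisting acupuncture"), and that intended sensation should not be logged as an event.

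Expectedness and duration may then be used to classify events already recorded. A table split by duration is optional. It would need no new data, since onset, duration and severity are already on the report.

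The change is to the wording of two sentences. It brings more minor events for staff to log and for the panel to evaluate, and possibly a less favourable reported rate. The Trial status section gives recruitment as running from January to December 2013, so the change may need an amendment. Events before and after it should then be reported separately, which leaves two ascertainment periods within an arm of 20.

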### Usual care control group

The control group will be allowed to use any type of treatment for dry eye symptoms: artificial tear drops, drugs, supplements (for example, cyclosporine, corticosteroids, and autologous serum), and alternative treatments other than those listed above as exclusions. Patients will be followed-up every two weeks and asked to report any change in medical history or drug use at each visit.

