### General assessment

A general assessment will be carried out in which both practitioners and participants will assess the improvement in symptoms related to dry eye syndrome after acupuncture or the conventional treatment regimen. The patient’s condition will be graded as excellent, good, fair, no change, or aggravated (Table 2).

**Table 2 T2:** Evaluation plan

	**Screening**	**Treatment or observation**												**Assessment**	
**Week**		**1**			**2**			**3**			**4**			**5**^ **a** ^	**13**^ **b** ^
**Visit**	**1**	**2**	**3**	**4**	**5**	**6**	**7**	**8**	**9**	**10**	**11**	**12**	**13**	**14**	**15**
OSDI		**●**						**●**						**●**	**●**
VAS	**●**	**●**						**●**						**●**	**●**
Schirmer-I test	**●**														**●**
TBUT	**●**														**●**
Corneal surface photography	**●**														**●**
QOL		**●**						**●**						**●**	**●**
Drug or therapeutic modalities															**●**
General assessment														**●**	

^a^: 4 weeks after visit 2 + 3 days; ^b^: 12 weeks after visit 2 + 3 days; **●**: All groups.

OSDI: Ocular surface disease index; VAS: Visual analog scale; TBUT: Tear film break-up time; QOL: quality of life.

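### The adverse-event recording sentence is narrower than the definition beside it, and up to week 5 adverse events and co-treatment are collected by different rules in the two arms

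*Protocol article*

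**What the plan says.** The Adverse events section opens with a definition that does not depend on causality: "Adverse events are unexpected signs, symptoms or diseases encountered during the clinical trial, whether or not they are related to acupuncture treatment". It then lists examples of local, systemic and psychological events, several with a minimum duration. Its only statement of what is written down follows: "All unexpected responses related to acupuncture treatment will be recorded". After that, an outside panel "will evaluate any report of an adverse event", and the causality codes on each report include "4 = probably not related, 5 = definitely not related and 6 = unknown".

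The Intervention section gives each arm its own collection rule. For acupuncture plus usual care: "Any changes in medical history or vital signs and reports of adverse events will be recorded at every follow-up visit". For usual care alone: "Patients will be followed-up every two weeks and asked to report any change in medical history or drug use at each visit".

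Under the heading on the efficacy of drug or other treatment, all participants are reminded from visit 14 of what they may use and are asked to keep a diary of changes in history or treatment, collected at visit 15. In Table 2 the row "Drug or therapeutic modalities" has a single mark, at visit 15, and the legend applies the marks to all groups. The Discussion part of the Abstract names safety, alongside effectiveness, as something the trial will inform.

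**The concern.** There are two separate problems.

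First, staff who follow the recording sentence and staff who follow the definition would fill in different case report forms. Under the narrower rule, an event judged unrelated need not be written down, and someone has to make that judgement before anything is recorded. In a comparison with an arm that gets no needling, that judgement cannot be made even-handedly.

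Second, the number of events found depends on how often and how directly people are asked. If one arm is asked about adverse events at frequent visits and the other is asked about history and drugs every two weeks, part of any difference in event counts comes from the asking. The same applies to co-treatment. Both arms may use nearly any dry-eye treatment, and participants know whether they are being needled. A change in drops or drugs in one arm is thus an obvious rival explanation for an OSDI difference, and a matched record is needed to examine it.

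**Working it through.** The plan states no figure on this point, so there is none to reproduce. The check sets the texts side by side and counts contacts.

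**1. Inside the Adverse events section**

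| Element | Scope |
|---|---|
| Definition | Unexpected events, related or not |
| Recording sentence | Unexpected responses that are related |
| Panel review | Any report |
| Causality code | Includes probably and definitely not related |

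Three of the four elements cover unrelated events and one does not. The word *unexpected* limits both the definition and the recording sentence, although the section's own examples (swelling, redness, bruising, pain) are foreseeable effects of needling.

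**2. Between arms, as stated**

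| Item | Acupuncture plus usual care | Usual care |
|---|---|---|
| Medication and drops at screening (Recruitment) | Yes | Yes |
| Change in medical history | Named | Named |
| Adverse events | Named, every follow-up visit | Not named |
| Vital signs | Named, every follow-up visit | Not named |
| Drug use before visit 14 | Not named | Named, two-weekly |
| Treatment diary, visit 14 to 15 | Yes | Yes |

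**3. Contacts from visit 2 to visit 14**

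- Acupuncture: treatment visits 2 to 13 are 12 contacts, and visit 14 makes 12 + 1 = 13. This assumes that each session counts as a follow-up visit.
- Control: two-weekly contact from visit 2 falls at weeks 1, 3 and 5, which are visits 2, 8 and 14, so 3 contacts. This mapping is also an assumption.
- Ratio: 13 / 3 = 4.3.
- Leaving out visit 2 in both arms as the baseline visit: 12 against 2, ratio 12 / 2 = 6.
- If only the assessment visits 8 and 14 count as follow-up in the acupuncture arm: 2 against 2, ratio 1.

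The imbalance in frequency therefore lies between 1 and 6, depending on what a follow-up visit is. Even at a ratio of 1, the items named for the two arms still differ.

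**4. Overlap with the primary outcome**

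OSDI is taken at visits 2, 8, 14 and 15, so there are three assessments after baseline. Two of them (visits 8 and 14) come before the common diary, which is read here as starting at visit 14. For those two, the text gives no co-treatment record that is the same in both arms.

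**The case against.** The strongest reply is that the section, read whole, intends full recording. The recording sentence promises to capture all of a class of events and does not say that nothing else is captured. The definition, the panel's remit and the codes for unrelated events would be pointless if unrelated events were dropped. The acupuncture-arm rule sets no relatedness limit either. This stands. A reader might infer that only acupuncture-related responses are kept and that no control-arm event could ever qualify, but the text does not say so. What remains is an inconsistency that staff could resolve either way.

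A reader might also infer that ordinary needling effects are excluded as expected, or that short-lived bruising is lost because of the duration thresholds. Neither is supported. The section itself lists needling effects as adverse events, the local list is introduced as examples, and each report captures duration and a mild grade. The wording is loose, but it does not exclude these events.

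It can fairly be said that denser contact is inherent in comparing thrice-weekly sessions with usual care, that no between-arm test of adverse events is planned in the Statistical analysis section, and that a condensed article may leave common forms to the full protocol. The first two points limit the weight of the finding. The third would settle it if the article were merely silent. But the article states a rule for each arm, and the two rules differ.

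Finally, one might argue from sample size: with 0 events in 20 patients the exact two-sided 95% upper limit is 1 − 0.025^(1/20) = 0.168, or 16.8%. The arithmetic is right, but the limit follows from 20 per arm and is the same before and after any change to recording. It does not measure this defect.

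**Conclusion.** The point holds in two limited parts. The recording sentence conflicts with the definition and the causality scale in its own section, and the conflict must be reconciled. Up to week 5, the stated rules give unequal ascertainment of adverse events and no matched co-treatment record, so comparisons of either are open to bias in that period.

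On the plain mapping the acupuncture arm has about four times as many contacts; the range is 1 to 6 under the assumptions shown. The resulting bias cannot be sized, because the article gives no event or co-treatment rates.

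It would be going too far to conclude that safety and co-treatment cannot be compared at all. Changes in history are asked about in both arms, medication is recorded for everyone at screening, and the diary from visit 14 to visit 15 is common to both arms. The conclusion rests on the arm-specific rules being applied as written. A common case report form in the full protocol would remove most of the second part, but not the contradiction in wording. This is worth correcting, but it does not undermine the design.

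**What to change.** - **Recording rule.** Replace the recording sentence with a statement that every untoward event is recorded in both arms, with relatedness, expectedness and duration entered as coded attributes and not used as conditions for entry. Align the definition with it.
- **Adverse events.** Ask one identical question in both arms at visits 8, 14 and 15. Visit 2 is the pre-treatment baseline and is not suitable for it.
- **Co-treatment.** Ask one identical question on dry-eye drugs and other treatments in both arms at visits 2 (as baseline), 8, 14 and 15.
- **Table 2.** Add an adverse-event row and extend the treatment row to show these visits.
- **Analysis.** Base any between-arm comparison on the common visits, and report events noted at the additional acupuncture sessions separately.

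All these visits are already scheduled for both groups, so the cost is protocol and form wording and a few minutes per visit. The drawback is a slightly longer form and a longer adverse-event listing. The article says that recruitment has begun, so if the change comes partway, the date of the new form should be recorded and data from before and after it kept distinguishable.
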